## Abstract

**Introduction:** Rheumatoid arthritis (RA) is a globally challenging and refractory autoimmune disease, constituting a serious menace to human health. RA is characterized by recurrent pain and is difficult to resolve, necessitating prolonged medication for control. Yishen Tongbi decoction is a traditional Chinese herbal compound prescribed for treating RA. We have completed a 3-year RCT study that confirmed the clinical efficacy of Yishen Tongbi decoction for RA. Notably, we observed a faster clinical remission rate compared to MTX by week 4 of treatment. In our forthcoming study, we intend to conduct a comprehensive assessment of the efficacy and safety of Yishen Tongbi decoction in the real-world treatment of RA through a prospective study.

**Methods and analysis:** This prospective, multicenter, real-world observational study will be conducted at two designated centers in China from October 2023 to August 2025. The study will include 324 patients with active rheumatoid arthritis. One group will receive Yishen Tongbi decoction combined with conventional synthetic disease-modifying antirheumatic drugs (csDMARDs). The other group will receive standard treatment. Standard treatment can be further divided into subgroups: csDMARDs, targeted synthetic disease-modifying antirheumatic drugs (tsDMARDs), and biologic disease-modifying antirheumatic drugs (bDMARDs). In each group, the number of tender joints, number of swollen joints, pain score, patient global assessment, physician global assessment, disease activity index (DAS28-ESR or DAS28-CRP), clinical disease activity index (cDAI), simplified disease activity index (sDAI) and relevant laboratory data will be compared. Clinical indicators and disease activity of the patients will be assessed at baseline, week 4 and week 12 after the initiation of treatment. The primary outcome will be the American College of Rheumatology 20% improvement criteria (ACR20) attainment rate among patients at week 12 after treatment. Every adverse event will be reported.

**Ethics and dissemination:** This study has been approved by the Ethics Committee of the first affiliated Hospital of Guangzhou University of traditional Chinese Medicine (NO.K-2023-009). The results of the study will be published in national and international peer-reviewed journals and at scientific conferences. The researchers will inform participants and other RA patients of the results through health education.

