### Objective

Based on previous RCT studies on YSTB, we will initiate a prospective real-world study to comprehensively assess the efficacy and safety of YSTB in RA treatment. Subgroup analyses will be used to evaluate the clinical remission effectiveness in RA patients receiving various treatment strategies. Furthermore, we will assess whether the combination of YSTB can provide additional significant beneficial results on the basis of csDMARDs.

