### Sample size estimation

Based on previous study and physician experience (Xu et al., 2023), this study comprises two independent trials with comparative rates. Its objective is to explore whether there exists a disparity in the ACR20 response rate between the two groups after 12 weeks of treatment. The prior study conducted by our research group indicated that after 12 weeks of treatment, the ACR20 response rate was 87% for the YSTB combined with the MTX group, while it was 74% for the MTX group. Assuming *α* = 0.05 (two-tailed test) and achieving a power of (1-β) = 0.8, we utilized PASS 15 software to calculate sample sizes for the experimental and control groups, totaling 324 patients to be included.

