### Interventions

This observational study is to evaluate the efficacy and safety of YSTB in the real-world hospital setting. Therefore, for the enrolled participants, there is no strictly defined treatment regimen. After evaluating the patient’s condition, the doctor chooses the most appropriate therapeutic medication treatment medication. Patients who receive YSTB (150 mL orally once a day) combined with csDMARDs to manage their condition will be divided into YSTB combined with csDMARDs group. Patients who are treated with bDMARDs/tsDMARDs, along with csDMARDs, or those using a combination of two csDMARDs, will be placed in the standard treatment group. As for specific drugs, common csDMARDs may include medications like Methotrexate, Leflunomide, or Apremilast, while tsDMARDs could consist of drugs such as Tofacitinib tablets or Baricitinib tablets. bDMARDs may include medications like Yisaipu. Nonsteroidal anti-inflammatory drugs (NSAIDs) or oral corticosteroids (prednisone ≤10 mg/days or the same dose) can be added when necessary. The medication information of the participants will be recorded in the case report form (CRF) at each follow-up.

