### Statistical analyses

Attempting to ensure equivalence in baseline characteristics of participants between the YSTB group and the conventional therapy group, a propensity score method will be performed. Variables involving age, sex, smoking history, BMI and other factors will be included into the logistic regression model to calculate a propensity score for each participant. Participants who used YSTB will be matched to those who receive conventional drugs alone based on the propensity score, using the greedy matching with a standard calliper width of 0.2 and without case replacement. Covariate balance of the matched cohort will be assessed using the mean standardized differences. When a |d| > 0.10, it is considered as an imbalance. Inverse probability of treatment weighting based on the propensity score will also be performed to evaluate the robustness of the matching results. Baseline demographic variables will be presented as means, medians, or percentages, and using Chi-square test, independent *t*-test, or Mann-Whitney *U* test, as appropriate. Outcomes of CDAI, SDAI, DAS-28, ACR20, ACR50, ACR70 will be analyzed by using Chi-square test and logistic regression. Odd ratios and 95% confidence intervals will be estimated. Subgroup analysis will be performed on age, gender, treatment regimens (CHM alone, conventional medication alone and the combination). All analysis will be tested with a two-sided alpha level of 0.05 except the logistic regression. For the missing data, the reasons why the data is missing will be analyzed, and multiple imputation will be used.

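### The planned regimen subgroups do not fit the study groups, and the pooled control group cannot give the add-on effect on which the study was sized

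*Protocol article*

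**What the plan says.** All places are in the protocol article.

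- **Objective.** After a general assessment of YSTB and subgroup analyses by treatment strategy, it adds that "we will assess whether the combination of YSTB can provide additional significant beneficial results on the basis of csDMARDs".
- **Sample size estimation.** The planning rates come from an add-on contrast on one csDMARD: "the ACR20 response rate was 87% for the YSTB combined with the MTX group, while it was 74% for the MTX group". The error rates are α = "0.05 (two-tailed test) and achieving a power of (1-β) = 0.8", "totaling 324 patients to be included".
- **Interventions.** Patients who receive YSTB "combined with csDMARDs to manage their condition will be divided into YSTB combined with csDMARDs group". How many csDMARDs they take is not fixed. Patients on a b/tsDMARD with csDMARDs, or "those using a combination of two csDMARDs, will be placed in the standard treatment group". Study design and the Figure 1 legend define the control group in the same way.
- **Abstract.** "Standard treatment can be further divided into subgroups: csDMARDs, targeted synthetic disease-modifying antirheumatic drugs", with biologics as the third class.
- **Statistical analyses.** YSTB users are matched by propensity score to all users of conventional drugs. The only regimen analysis given is this: "Subgroup analysis will be performed on age, gender, treatment regimens (CHM alone, conventional medication alone and the combination".
- **Discussion.** The stated aim and hypothesis are that YSTB plus csDMARDs is non-inferior to standard treatment, described there as the same pool of two regimen types.

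**The concern.** There are two separate defects.

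First, the three regimen levels look like a classification for a different study. If one level has no patients and the other two are the treatment groups, the analysis adds nothing to the main comparison. It also leaves the comparisons by treatment class, which the Abstract and Objective announce, without an analysis that could produce them.

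Second, the article uses three comparators as if they were one: methotrexate alone (sample size), csDMARDs as a background (Objective), and a pool of dual csDMARDs and b/tsDMARD combinations (Interventions). A pooled odds ratio against the third may be read as the benefit of adding YSTB to csDMARDs, which it is not. Its value would also move with the regimens that the two centres happen to prescribe, even if every regimen-specific response rate stayed the same.

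**Working it through.** **1. Regimen levels against group definitions**

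| Level in Statistical analyses | Who could be in it under Interventions |
|---|---|
| CHM alone | Nobody: YSTB defines a group only together with csDMARDs |
| Conventional medication alone | The whole standard treatment group |
| The combination | The whole YSTB plus csDMARD group |

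The Inclusion criteria point the same way, since they require standard RA treatment to have been maintained for at least 4 weeks. No level separates csDMARD controls from b/tsDMARD controls.

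**2. Patients without a group**

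The Introduction calls methotrexate the current standard treatment, so a patient on methotrexate alone can meet the Inclusion criteria. Interventions places such a patient in neither group. The 74% in the sample size is therefore the rate of a regimen that the control definition leaves out.

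**3. The stated sample size**

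Inputs: p1 = 0.87, p2 = 0.74, difference 0.13, two-sided α 0.05, power 0.80. Equal groups are assumed, because allocation is not stated.

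n = [1.96·√(2·0.805·0.195) + 0.8416·√(0.87·0.13 + 0.74·0.26)]² / 0.13² = (1.0982 + 0.4652)² / 0.0169 = 144.6, so 145 per group and 290 in total.

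With continuity correction the result is 160 per group, 320 in total, within 3% of 324. Without it, a 10% dropout allowance (not in the text) gives 145/0.9 = 161.1, so 162 per group and exactly 324. The figure is thus reproducible from 87% vs 74%. At 162 per group the power is Φ[(0.13 − 1.96·0.0440)/0.0434] = 0.84, provided that the whole control group responds at 74%.

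**4. Dependence of the pooled contrast on the mix**

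Let w be the share of controls on a b/tsDMARD. The article gives neither w nor a b/tsDMARD response rate, so both are assumed. Applying the methotrexate rate of 74% to dual-csDMARD controls is also an assumption.

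Pooled difference = 0.87 − [0.74(1 − w) + 0.84w]:

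- w = 0: 0.87 − 0.74 = 13 points; odds ratio (0.87/0.13)/(0.74/0.26) = 2.35
- w = 0.5: 0.87 − 0.79 = 8 points; odds ratio (0.87/0.13)/(0.79/0.21) = 1.78
- w = 1: 0.87 − 0.84 = 3 points; odds ratio (0.87/0.13)/(0.84/0.16) = 1.27

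Varying the assumed b/tsDMARD rate as well gives the following differences in points, with power at 162 per group in brackets:

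| b/tsDMARD rate | w = 0.25 | w = 0.50 | w = 0.75 |
|---|---|---|---|
| 80% | 11.5 (0.76) | 10.0 (0.65) | 8.5 (0.53) |
| 85% | 10.25 (0.67) | 7.5 (0.44) | 4.75 (0.22) |
| 90% | 9.0 (0.57) | 5.0 (0.24) | 1.0 (0.05) |

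These powers are for a two-sided test of a difference, as in the sample size section. If both control types respond at 74%, the mix has no effect: 13 points, power 0.84.

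**5. Precision of a csDMARD-only contrast**

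For 87% vs 74% with half of 162 controls (81) on csDMARDs:

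- All 162 YSTB patients kept: pooled rate (162·0.87 + 81·0.74)/243 = 0.827; standard error 0.0515 under the null and 0.0554 under the alternative; power Φ[(0.13 − 1.96·0.0515)/0.0554] = 0.70.
- 1:1 matching, 81 vs 81: standard errors 0.0623 and 0.0614; power Φ[(0.13 − 1.96·0.0623)/0.0614] = 0.55.

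At a 25% csDMARD share the two powers are 0.53 and 0.31; at 75% they are 0.79 and 0.73.

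**The case against.** The strongest reply is that the pooled contrast is the one that the study's hypothesis names. The Discussion defines standard treatment as this pool and hypothesises non-inferiority to it. A usual-care comparator always reflects local prescribing, and the add-on question comes last in the Objective. This stands. A reader might infer that the pooled estimate answers none of the study's questions, and the text does not support that.

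A reader might also infer that the add-on question has no comparator at all. That goes too far. Dual-csDMARD controls exist, and for any YSTB patients who also take two csDMARDs they are a true add-on comparator. For YSTB with one csDMARD, the contrast is YSTB in place of a second csDMARD. What remains is that no stated analysis isolates this stratum. Likewise, it is only single-csDMARD patients who have no group; dual-csDMARD patients do have one.

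Third, a journal article may leave subgroup detail to an analysis plan that is not shown. So the failure to repeat the three-class split is not in itself a fault. The fault is that the regimen levels which are stated conflict with the Abstract and with the group definitions.

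Finally, the empty level does not cause the mixing. The mixing comes from pooling the controls and matching to the whole pool, and deleting the subgroup sentence alone would not remove it.

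**Conclusion.** The regimen subgroup analysis is wrong as written: one level is empty and the other two repeat the main comparison. It cannot deliver the comparison by class named in the Abstract or isolate the add-on question. This follows from the text and needs no numerical assumption.

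The Objective and the sample size describe an add-on contrast that the pooled control group does not provide. The pooled estimate remains relevant to the non-inferiority hypothesis, but it depends on the control mix whenever the two control regimens respond differently. Non-inferiority to the pool would not by itself show non-inferiority to b/tsDMARDs.

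The 13, 8 and 3 points show direction and possible scale only, since the 84%, the mix, and the use of 74% for dual-csDMARD controls are all assumed. A reader might also infer that 324 is miscalculated. It is not; it simply applies to a contrast other than the pooled one.

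**What to change.** 1. In Statistical analyses, replace the three regimen levels with contrasts by comparator class on week-12 ACR20: YSTB plus csDMARD against csDMARD controls, and YSTB plus csDMARD against b/tsDMARD plus csDMARD controls. Give each its own propensity score, because the reasons for choosing YSTB may differ between the two comparators.
2. Keep the pooled contrast for the hypothesis in the Discussion. Report the control mix as enrolled and after matching and weighting. State which contrast is primary.
3. Reconcile Objective, Sample size estimation and Interventions. If csDMARD controls remain on two csDMARDs, either restrict the add-on claim to YSTB patients who also take two, or reword the objective as YSTB in place of a second csDMARD. State how eligible patients on a single csDMARD are handled.
4. Do not present 87% vs 74% as the expected difference for the pooled group.

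Cost: changes of wording, a second propensity model and lower precision per contrast. With half the controls on csDMARDs (assumed), power for 87% vs 74% is about 0.70 with 162 vs 81 and about 0.55 if matched 1:1, and lower still with a smaller csDMARD share. The class-specific contrasts should therefore be reported as estimates with confidence intervals.

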## Discussion

There are three clinical problems in RA that need to be solved urgently: 1) the pathogenesis is complex, and it is difficult to diagnose and treat early. 2) lack of high-efficient and low-toxic drugs, and the therapeutic mechanism of traditional Chinese medicine is unknown. 3) the therapeutic advantages of traditional Chinese medicine lack of high-quality research evidence. Therefore, on the basis of explaining the pathogenesis and core pathological targets of RA, it is very necessary and urgent to establish new strategies for the treatment of traditional Chinese medicine and develop new drugs with high efficiency and low toxicity.

YSTB is a patented Traditional Chinese Medicine (TCM) formulation used for the treatment of RA for over a decade. Previous RCT studies have shown that YSTB has a quick effect, which is not inferior to methotrexate, and has fewer side effects. Current standard RA treatments include bDMARDs/tsDMARDs along with csDMARDs, or a combination of two csDMARDs. The combined use of csDMARDs may cause bone marrow suppression and hepatorenal toxicity (Drosos et al., 2020; Yates et al., 2020). The application of tsDMARDs in individuals with low immunity, particularly the elderly, can lead to herpes zoster infections and increased thrombotic risks (Fujii et al., 2024). The high cost of bDMARDs restricts their use and may activate latent infections like tuberculosis or hepatitis, as well as increase the risk of tumor development (Chatzidionysiou et al., 2017). In light of these issues, we embarked on a real-world study to develop safe, effective TCM compounds with minimal side effects. The aim is to establish YSTB in combination with csDMARDs as a treatment option that is not inferior to standard treatments and offers superior safety and cost-effectiveness.

The theory of traditional Chinese medicine and the practice of doctors of previous dynasties have shown that the cause of RA is the deficiency of liver and kidney, exogenous wind, cold, dampness and heat, which finally leads to the obstruction of meridians. Combined with the theory of traditional Chinese medicine and long-term clinical practice, our research group developed “Yishen Tongbi decoction” for the treatment of RA with “Bushen Tongluo” as the specific treatment. The prescription is composed of *L. lucidum* W.T.Aiton 15 g, *E. prostrata* (L.) L. 15 g, *E. ulmoides* Oliv. 15 g, *L. barbarum* L. 15 g, *S. miltiorrhiza* Bunge 15 g, and *T. wilfordii* Hook. f. 25 g. Combined with the contemporary theory of “medicine group” (Du, 2010), the four groups of *L. lucidum* W.T.Aiton, *E. prostrata* (L.) L., *E. ulmoides* Oliv. and *L. barbarum* L. were used to tonify the liver and kidney and strengthen the muscles and bones. According to the principle of “treating as a king and treating as a minister” (Wei et al., 2014), *S. miltiorrhiza* Bunge mainly promotes blood circulation and removes blood stasis, relieves menstruation and relieves pain, *T. wilfordii* Hook. f. mainly dispels wind and dehumidification, relaxes muscles and activating collaterals, the above two flavors are subject medicine group, take its blood circulation and dredge collaterals to relieve pain. The party and its preparation process have been authorized by the national invention patent (ZL2010110191532.X). *Tripterygium wilfordii* Hook.f. has been proved to have strong anti-inflammatory and immunosuppressive effects by many clinical and basic studies, which can significantly improve joint swelling and pain and delay bone destruction in patients with RA (Zhang et al., 2007; Zhao et al., 2014; Xie et al., 2015; Chen et al., 2018). *Ligustrum lucidum* W.T.Aiton and its extract can improve bone metabolism and inhibit osteoclast differentiation so as to achieve the effect of anti-osteoporosis (Chen et al., 2017). The ethanol extract of *E. ulmoides* Oliv. can inhibit the secretion of pro-inflammatory cytokines, promote the secretion of anti-inflammatory cytokines, inhibit the proliferation of synovial cells and delay the degradation of chondrocytes and bones, all of which can improve the symptoms of RA (Wang et al., 2016). *Lycium barbarum* L. has immunomodulatory, anti-inflammatory and anti-osteoporotic effects in the treatment of RA (Cheng et al., 2015). Studies have shown that *S. miltiorrhiza* Bunge has specific anti-inflammatory and anti-immune effects, which can significantly improve the related symptoms of mice (Gao et al., 2012). *Eclipta prostrata* (L.) L. and its active components inhibit the proliferation and differentiation of RAW264.7 osteoclasts at low doses. These results suggest that *E. prostrata* (L.) L. may be used in the treatment of osteoporosis (Liu et al., 2014).

Traditional Chinese medicine theory, clinical practice and many basic studies have shown that Yishen Tongbi decoction has a significant effect in the treatment of RA, but the therapeutic advantage of traditional Chinese medicine is still lack of high-quality evidence-based medicine. Therefore, the research group conducted a double-blind, randomized, controlled, non-inferiority trial of YSTB in the treatment of active RA, head-to-head comparison of the efficacy and adverse reactions of MTX (Xu et al., 2023). This clinical trial is the first RCT study in China to use traditional Chinese medicine compound prescription and MTX to conduct a head-to-head study in the field of RA treatment. This study uses CDAI as the main outcome index for a period of 24 weeks. The results showed that the standard rate of CDAI in YSTB group and MTX group were 67.4% (33/49) and 57.1% (28/49), respectively, and the risk difference was 0.102 (95% CI −0.089 to 0.293), indicating that Yishen Tongbi decoction was not inferior to MTX. In the secondary outcome index, compared with the MTX group, the YSTB group had a higher rate of good or moderate response to ACR20 (57.1% vs. 30.6%, *p* = 0.008) and good or moderate response to EULAR (61.2% vs. 34.7%, *p* = 0.009) at week 4, suggesting that YSTB took effect faster than MTX. The incidence of drug-related adverse events was 28.6% (14/49) and 22.4% (11/49) in the YSTB and MTX groups, respectively. There was no significant difference in the incidence of drug-related adverse reactions between the two groups (*p* = 0.487), and there was no serious non-reaction, which proved the safety of YSTB. Both YSTB and MTX groups showed impaired liver function (ALT >33 U/L) as the most frequent drug-related side effect, with rates of 14.3% (7/49) and 12.2% (6/49) respectively (*p* = 0.766). Although liver function abnormalities were more common than other adverse events, 4 patients in each group had slightly elevated levels (<2 times the upper limit), mostly asymptomatic, allowing trial completion. One YSTB patient with ALT of 123 U/L at week 12 normalized with outpatient liver protection. Gastrointestinal reactions occurred in 2.0% (1/49) in both groups (*p* = 1.000). Diarrhea led to study discontinuation in one patient per group, and one YSTB patient stopped due to paroxysmal palpitations. Leukopenia incidence was 2.0% in both groups, and one MTX patient appeared anemic. Menstrual irregularities affected 3.5% (3/86) of female patients (43 premenopausal) without significant group difference (*p* = 0.554) during the 24-week trial (Xu et al., 2023). This study provides high-quality evidence of evidence-based medicine for the treatment of RA with YSTB, and the relevant results are published in the first District Journal of the highest influencing factor in the field of traditional Chinese medicine.

Although RCT is the gold standard for evaluating the safety and effectiveness of interventions, it has some limitations, such as strict inclusion and exclusion criteria, relatively small sample size, poor external authenticity, and high difficulty and cost of implementation. Real-world study (RWS) is a continuation and supplement of RCT, which aims to evaluate the actual efficacy of interventions in the real diagnosis and treatment environment under a large sample size, emphasizing external authenticity, and is widely used in disease diagnosis and treatment, prognosis and etiological analysis. High-quality RWS can accelerate the approval of new drugs and new indications (Knottnerus and Tugwell, 2010) In addition, the previous RCT study is a single-center study, a total of 82 patients completed the trial, the sample size is small, the multicenter trial with larger sample size is needed to obtain more objective clinical data for verification. Based on the above two points, our research group plans to carry out real-world study on the treatment of active RA patients with YSTB, in order to provide high-quality evidence-based medicine for the treatment of RA with traditional Chinese medicine compound, and promote the research and development of new drugs with low toxicity and high efficiency against RA.

Our research also has some limitations. First of all, there are subjective indicators evaluated by patients and doctors in the study. Therefore, these results may be biased. We can only assume that doctors maintain relatively uniform evaluation criteria and patients need further guidance on how to correctly assess the disease. Secondly, due to various reasons, it may be difficult for patients to adhere to the 12-week study cycle, so it is necessary to strengthen follow-up and timely communication with patients to minimize the drop-out rate. After the completion of the trial, we hope to make a clear conclusion on the efficacy and safety of YSTB.

Drawing upon past clinical experience and RCT studies, we hypothesize that YSTB combined with csDMARDs is not inferior in efficacy to the standard treatment group, offers better safety, and is more cost-effective. This research aims to offer more treatment options for RA patients. We have conducted RCT research on the treatment of RA with YSTB compound formulas and are planning to carry out a real-world study, aiming to provide more comprehensive data on YSTB. In the future, we intend to design comparative studies between YSTB decoction and granules, as well as develop hospital preparation and new drug launches, aiming to benefit more RA patients with YSTB.

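### The study is sized and tested for a difference in ACR20, but the Discussion states a non-inferiority hypothesis without a margin or decision rule

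*Protocol article*

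**What the plan says.** Three sections describe a study of difference.

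- Objective asks whether adding YSTB to csDMARDs brings a significant further benefit.
- Sample size estimation says: "Its objective is to explore whether there exists a disparity in the ACR20 response rate between the two groups after 12 weeks of treatment". Its inputs are that "the ACR20 response rate was 87% for the YSTB combined with the MTX group, while it was 74% for the MTX group", with α = "0.05 (two-tailed test) and achieving a power of (1-β) = 0.8". The result is stated as: "we utilized PASS 15 software to calculate sample sizes for the experimental and control groups, totaling 324 patients to be included".
- Statistical analyses plans a chi-square test and logistic regression for ACR20, with odds ratios and 95% confidence intervals. It adds: "All analysis will be tested with a two-sided alpha level of 0.05 except the logistic regression".

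The Discussion describes a study of non-inferiority. It first gives the aim as establishing YSTB plus csDMARDs as a "treatment option that is not inferior to standard treatments and offers superior safety and cost-effectiveness". Its closing part then puts this as the formal hypothesis: "we hypothesize that YSTB combined with csDMARDs is not inferior in efficacy to the standard treatment group, offers better safety, and is more cost-effective".

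The article gives no non-inferiority margin, no rule comparing a confidence limit with a margin, and no one-sided test.

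**The concern.** A test of difference and a test of non-inferiority answer different questions. Failing to reject equality is not evidence that YSTB is no worse than standard treatment by some tolerable amount. That needs a margin fixed in advance and a confidence limit compared with it.

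The gap cannot simply be left to an analysis plan that is not shown. In a non-inferiority design the margin determines the sample size, and the article reports a completed sample size calculation that uses none.

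At stake is the primary conclusion. If YSTB is significantly better, the conflict does no harm. In any other case the stated hypothesis has no rule by which it could be accepted or refused, and the readiest misuse is to report a non-significant chi-square test as showing non-inferiority. Fewer patients make a non-significant result more likely when a true difference exists. Calliper matching without replacement and dropout both work in that direction.

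**Working it through.** **Inputs.** Response rates 0.87 and 0.74, two-sided α 0.05, power 0.80 and total 324 come from Sample size estimation. Three things are assumed here: 1:1 allocation (162 per group), no loss to matching or dropout, and control rates from 74% to 87%, which are the article's own two figures.

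**1. Reproducing 324.** Pooled two-sided formula, mean rate 0.805:

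n = [1.96·√(2·0.805·0.195) + 0.8416·√(0.87·0.13 + 0.74·0.26)]² / 0.13² = (1.0982 + 0.4652)² / 0.0169 = 144.6, so 145 per group, 290 in total.

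- With continuity correction: 160 per group, 320 in total.
- Without correction but with a 10% dropout allowance, which the article does not state: 145/0.9 = 161.1, so 162 per group, 324 in total.
- One-sided versions give 228, or 258 with correction.

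The figure of 324 is therefore consistent with a two-sided test of difference. No margin is needed to reach it.

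**2. Largest deficit that stays non-significant.** Solve d = 1.96·√[2·p̄(1−p̄)/162], where p̄ is the mean of the control rate and the control rate minus d. The lower 95% limit is −d − 1.96·SE, with SE unpooled.

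| Control rate | d | SE | Lower 95% limit |
|---|---|---|---|
| 74% | 10.1 points | 0.0511 | −20.1 points |
| 87% | 8.2 points | 0.0416 | −16.4 points |

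**3. How often a truly worse YSTB escapes detection.** With 162 per group and a control rate of 74%, the two-sided test has power 0.494 if the true YSTB rate is 64%, so it is non-significant about 51% of the time. At a true rate of 69% the power is 0.167, so it is non-significant about 83% of the time.

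**4. What 324 patients give as a non-inferiority design.** Equal true rates p, one-sided 0.025: power = Φ(margin/SE − 1.96), SE = √[2p(1−p)/162].

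| True rate in both groups | SE | 10-point margin | 15-point margin |
|---|---|---|---|
| 74% | 0.0487 | Φ(2.052 − 1.96) = 54% | Φ(3.078 − 1.96) = 87% |
| 87% | 0.0374 | Φ(2.676 − 1.96) = 76% | Φ(4.014 − 1.96) = 98% |

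For 80% power a 10-point margin needs 606 patients in total at 74%, or 356 at 87%. A 15-point margin needs 270 or 158. Whether 324 is enough depends wholly on the margin that is missing.

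**The case against.** The best defence is that the operative sections agree with one another. Objective, Sample size estimation and Statistical analyses all concern a difference, and the non-inferiority wording appears only in the Discussion. This is right. It makes the repair simpler, but the Discussion still labels non-inferiority as the study's hypothesis, so the conflict stands.

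A reader might infer more than the article supports, in four ways.

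- *That the investigators will treat a non-significant chi-square test as non-inferiority.* The article does not say so. For efficacy in their previous trial, the Discussion bases non-inferiority on a risk difference with a 95% interval (0.102, −0.089 to 0.293). The same section does read a non-significant adverse-event comparison (p = 0.487) as proof of safety, so the risk of misreading is real, but it remains a risk.
- *That nothing planned could show non-inferiority.* A significant result in favour of YSTB would show it at any margin, and the planned 95% intervals are the right tool once a margin exists.
- *That the cost-effectiveness and safety parts of the hypothesis are refuted.* The list of case report form contents is not shown to be exhaustive, so missing cost items prove nothing. The previous trial's adverse-event rates (28.6% against 22.4%) compared YSTB alone with MTX alone and did not differ significantly. The comparison here is a different one.
- *That exempting logistic regression from the 0.05 level leaves it with no level at all.* The 95% intervals for the odds ratios set one. The sentence is unclear, but that is a separate and minor matter.

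**Conclusion.** The contradiction is real and lies within the article: the study is framed, sized and tested for a difference, while the Discussion hypothesises non-inferiority with no margin or confidence-limit rule. Unless superiority is shown, the stated hypothesis cannot be concluded from the stated analysis.

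The size is material. An observed deficit of about 8 to 10 points would pass as non-significant while the data remained compatible with a deficit of about 16 to 20 points. Non-inferiority power ranges from 54% at a 10-point margin (rates of 74%) to 98% at 15 points (rates of 87%).

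These figures rest on 162 per group, no loss to matching or dropout, unadjusted proportions and, for non-inferiority power, equal true rates. A real advantage for YSTB would make non-inferiority easier to show: with true rates of 87% and 74%, 150 patients would do at a 5-point margin. But the 74% was observed on MTX alone, whereas Interventions defines the comparator as two csDMARDs, or a bDMARD or tsDMARD with csDMARDs, so the article gives no direct basis for expecting that advantage here.

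**What to change.** State one primary hypothesis and use it throughout. Either of two routes works.

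(a) Keep the difference test that was sized. Replace the non-inferiority wording at both places in the Discussion with that hypothesis. Report the ACR20 effect with its 95% interval; a risk difference may be added to the planned odds ratio. State that a non-significant result will not be reported as non-inferiority.

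(b) Keep non-inferiority. Fix and justify a margin on the ACR20 risk-difference scale before outcome data are examined. Draw the conclusion from the lower limit of the two-sided 95% interval, and state the power that 324 patients give at that margin.

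Separately, clarify or delete the exemption of logistic regression from the 0.05 level in Statistical analyses.

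Route (a) costs only wording and a narrower permitted conclusion. Route (b) also needs a justified margin and a restated power, which may prove to be below 80%.
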